## Introduction

### Background and rationale {6a}

#### Acute respiratory distress syndrome (ARDS)

ARDS is a common pathology seen in intensive care units globally, with associated significant mortality and even long-term morbidity. ARDS is a clinical diagnosis accounting for up to 20% of unplanned ICU admissions. Mortality in ARDS patients is still high. The LUNG SAFE study [Belani2016] reports a hospital mortality of 40%, with a significant increase across the ARDS severity categories, in line with Berlin definition (34.9%, in mild ARDS; 40.3% in moderate ARDS; 46.1% in severe ARDS). The socioeconomic burden of the disease of critical illness is immense. A recent systematic review regarding the endpoint “return to work after critical illness” reported that approximately two-thirds, two-fifths, and one-third of previously employed intensive care unit survivors are jobless up to 3, 12, and 60 months following hospital discharge [1].

The most recent Berlin definition of ARDS [2] is shown in Table 1. The pathophysiology of ARDS is not completely understood. Initially, a direct pulmonary or indirect extrapulmonary insult is believed to cause a release of inflammatory mediators that promotes neutrophil accumulation in the microcirculation of the lung. Activated neutrophils migrate in large numbers across the vascular endothelial and alveolar epithelial surfaces and release proteases, cytokines, and reactive oxygen species (ROS). The migration and mediator release of neutrophils lead to pathologic vascular permeability, gaps in the alveolar epithelial barrier, and necrosis of type I and II alveolar cells, resulting in pulmonary edema, hyaline membrane formation, loss of surfactant and ultimately alveolar collapse, ventilation/perfusion mismatch, decrease of pulmonary compliance, and altered gas exchange. Subsequent infiltration of fibroblasts can lead to collagen deposition, fibrosis, and worsening disease [3].

**Table 1 Tab1:** The Berlin definition of acute respiratory distress syndrome

Timing	Within 1 week of a known clinical insult or new or worsening respiratory symptoms
Chest imaging	Bilateral opacities—not fully explained by effusions, lobar/lung collapse or nodules ^a^
Origin of edema	Respiratory failure not fully explained by cardiac failure or fluid overload Need objective assessment (e.g., echocardiography) to exclude hydrostatic edema if no risk factor present
Oxygenation	

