Study 2012-001863-64 was a proof of concept study in male and female intensive care patients (*N* = 40; 1:1) that investigated the clinical effect of repeated orally inhaled doses of solnatide on alveolar liquid clearance in acute lung injury. For safety reasons and according to effective pharmacological doses observed in various animal models, the second highest dose of the Phase I clinical study was chosen: 125 mg solnatide (nebulizer filling dose) twice daily (i.e., every 12 h) delivered per endotracheal inhalation to each subject. The main efficacy outcome was a positive trend in pulmonary edema (EVLWI) reduction in the whole study population, which is significant and more pronounced in patients with an initial Sequential Organ Failure Assessment (SOFA) score above 10 inhaling solnatide versus placebo (*P* = 0.04; exploratory subgroup analysis). The secondary endpoint analysis revealed a trend towards an earlier improvement of peak, plateau and mean airway pressure, PEEP, and Murray lung injury score in patients treated with solnatide. This effect was again most prominent in patients with an initial SOFA score > 10 (exploratory subgroup analysis). In addition, a shorter duration of mechanical ventilation and increased number of ventilator-free days in patients receiving solnatide inhalations versus placebo was observed, which again was more pronounced in patients with initial SOFA score above 10 (*P* = 0.06; exploratory subgroup analysis). No significant differences in the occurrence of adverse events and severe adverse events were found between the study groups that could not be explained by the underlying diseases [23].

Study 2013-000716-21 was a pilot study that investigated the clinical effect of orally inhaled solnatide on treatment of primary graft dysfunction (PGD) in mechanically ventilated patients (*N* = 20; 1:1) after primary lung transplantation. When compared to placebo, oral inhalation of solnatide in patients with PGD following lung transplantation led to earlier improvement of gas exchange, reduction of EVLWI, earlier extubation / shorter mechanical ventilation, a shorter stay at the ICU, and earlier discharge from the hospital. No drug-related adverse events, drug-related serious adverse events, or deaths were reported.

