## Statistical methods

### Statistical methods for primary and secondary outcomes {20a}

Data collected in this study will be listed and summarized as described below by treatment group. Data from all sites will be pooled and summarized. Continuous data will be summarized by mean, standard deviation (SD), median, first and third quartiles, minimum, and maximum. Categorical data will be presented by absolute and relative frequencies (n and %) or contingency tables. All statistical tables, listings, figures, and analyses will be performed by means of SAS® release 9.4 or later (SAS Institute, Inc., Cary, NC, USA).

A two-sided alpha level 0.05 will be considered. No alpha level adjustment will be made for secondary preliminary efficacy outcome variables and for multiple comparisons. Patients will be included in each analysis based on available assessments. No methodology for missing data handling will be applied, except for the EVLWI efficacy endpoint. Censoring rules for time-to-event analyses will be detailed in the Statistical Analysis Plan.

There is no primary efficacy endpoint as the primary objective of the study is to investigate the safety of solnatide. All efficacy analysis will be considered as secondary preliminary efficacy analyses. All secondary preliminary efficacy analyses will be performed based on the ITT set as primary analysis and on the PP set as supportive analysis and will be reported by planned treatment cohort.

No methodology for missing data handling will be applied for secondary preliminary efficacy endpoints, except for EVLWI. The homogeneity of treatment effects across different centers will not be tested.

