#### Change from baseline to day 7 in extravascular lung water index (EVLWI)

The absolute change from baseline in extravascular lung water index (EVLWI) after 7 days from randomization, as assessed with a validated bedside measurement (single indicator transpulmonary thermodilution measurement, such as with PiCCO® from Pulsion or VolumeView from Edwards), will be analyzed by means of an analysis of covariance (ANCOVA) model with baseline value as covariate and treatment cohort as an independent class variable. Mean estimates will be provided, together with their corresponding two-sided 95% confidence intervals.

A hierarchical testing procedure will be carried out to control multiplicity, where statistical comparison will first be performed between the highest solnatide dose cohort and the placebo cohort. Statistical comparison between the next lower dose(s) and placebo will be performed only in case of statistical significance of the comparison between the highest solnatide dose cohort and the placebo cohort.

The analysis described above will be performed on data where the Last Observation Carry Forward approach is applied for handling missing data. Additional imputation methodologies for missing data may be applied as sensitivity analysis (further details to be provided in the Statistical Analysis Plan).
Secondary preliminary efficacy endpoints

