### Methods in analysis to handle protocol non-adherence and any statistical methods to handle missing data {20c}

Patients will be included in each analysis based on available assessments. No methodology for missing data handling will be applied, except for the EVLWI efficacy endpoint.

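### LOCF as the fixed main method for day-7 EVLWI can bias the contrast in a direction that depends on why values are missing, and no analysis that treats death separately is required

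*Protocol article*

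**What the plan says.** The section on the change in EVLWI defines the endpoint as "The absolute change from baseline in extravascular lung water index (EVLWI) after 7 days from randomization", measured by "single indicator transpulmonary thermodilution measurement, such as with PiCCO® from Pulsion or VolumeView from Edwards". It is analysed by ANCOVA with baseline EVLWI and treatment cohort. On missing values the section is explicit: "The analysis described above will be performed on data where the Last Observation Carry Forward approach is applied for handling missing data". Alternatives are permitted but not required: "Additional imputation methodologies for missing data may be applied as sensitivity analysis", with details left to the SAP. The section does not distinguish values missing through death, recovery, loss of the catheter or withdrawal.

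EVLWI is the only endpoint with any such rule; section {20c} says "No methodology for missing data handling will be applied, except for the EVLWI efficacy endpoint". Section {20a} adds that the efficacy analyses "will be performed based on the ITT set as primary analysis and on the PP set as supportive analysis". The highest dose is tested against placebo first, and lower doses are tested only if that comparison is significant.

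On who may be missing at day 7, the background gives hospital mortality of "40.3% in moderate ARDS; 46.1% in severe ARDS". For the earlier Phase IIa study in intensive care patients it reports that "a shorter duration of mechanical ventilation and increased number of ventilator-free days in patients receiving solnatide inhalations versus placebo was observed".

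**The concern.** LOCF gives the right day-7 mean only if nothing would have changed after the last measurement. That sits badly with a drug meant to move EVLWI over seven treatment days, and with a population in which death before day 7 is to be expected. Recovery is a second likely route to a missing value. The drug is expected to shorten ventilation, and a patient who no longer needs extensive haemodynamic monitoring may no longer have thermodilution.

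These two routes are opposite outcomes, yet the rule handles them identically. If their mix differs between arms, the estimate labelled as a day-7 difference combines the drug's effect on EVLWI with its effect on when measurement stops. Section {14} calls EVLWI the key preliminary efficacy endpoint, and the secondary objective is to review endpoints for a Phase III trial. Because of the testing order, a distorted result for the highest dose also decides whether the lower doses are tested.

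**Working it through.** **Inputs from the document (section {14}).** 20 evaluable patients per group, difference 3.2 ml/kg, SD 3.5, two-sided alpha 0.05, power about 80%.

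**The plan's own figure.** Noncentrality = 3.2 / (3.5 × √(2/20)) = 3.2 / 1.107 = 2.89 with 38 df, which gives power 80.4%. The stated figure reproduces.

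**Assumptions (not in the document).** Exit rates, exit days, the course of EVLWI and the placebo change. Positive differences favour solnatide.

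**Formula.** Let c be an arm's mean fall by day 7 if everyone were measured. If the fall is linear and a share m is last measured on day t, LOCF gives a mean fall of c × [1 − Σ m(1 − t/7)].

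*Patients leave while still falling:*
- 25% last measured on day 4 in both arms: 3.2 × (1 − 0.25 × 3/7) = 2.86.
- The same plus 10% last measured on day 2: 3.2 × (1 − 0.25 × 3/7 − 0.10 × 5/7) = 2.63.
- Day-4 exits of 35% on solnatide and 20% on placebo, plus 10% on day 2 in both, with placebo falling by 1 and solnatide by 4.2:
  - solnatide 4.2 × (1 − 0.35 × 3/7 − 0.10 × 5/7) = 3.27
  - placebo 1 × (1 − 0.20 × 3/7 − 0.10 × 5/7) = 0.84
  - difference 2.43
- Wider range, equal leaving in both arms: from 3.2 × (1 − 0.10 × 2/7) = 3.11 (10%, day 5) to 3.2 × (1 − 0.50 × 4/7) = 2.29 (50%, day 3).

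*No drug effect on EVLWI, only faster leaving:*
- Both arms fall by 4; 40% of solnatide and 20% of placebo patients are last measured on day 4: 4 × (0.40 − 0.20) × 3/7 = 0.34 ml/kg against solnatide.

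*Leavers have already plateaued:*
- The carried value equals the day-7 value, so the difference stays at 3.2.

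*More early deaths on placebo, with high last values (30% against 10%, placebo otherwise falling by 1):*
- Last value 2 ml/kg above baseline: solnatide 0.9 × (−4.2) + 0.1 × 2 = −3.58; placebo 0.7 × (−1) + 0.3 × 2 = −0.10; difference 3.48.
- Last value 4 ml/kg above baseline: solnatide −3.38; placebo 0.50; difference 3.88.
- Last value equal to baseline: solnatide 0.9 × (−4.2) = −3.78; placebo 0.7 × (−1) = −0.70; difference 3.08. Inflation therefore needs the high last values as well as the excess of deaths.

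**Would the alternative help?** Simulating the three linear-fall scenarios gives LOCF estimates of 2.87, 2.64 and 2.42. A repeated-measures model on the same data gives 3.18 to 3.22. In the no-effect case LOCF is off by about 0.36 and the model by about 0. These scenarios set exit by arm and day only, so they suit the model's missing-at-random assumption; they do not test it.

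**Power and standard errors.** In the same three scenarios power is 78%, 73% and 66% with LOCF against 77%, 71% and 69% with the repeated-measures model. A separate simulation (3,000 trials, 20 against 20, idealised model with known covariance) gives 75%, 68% and 63% against 71%, 65% and 64%. In that simulation the LOCF model standard error is close to the empirical SD of the estimate: 1.050 and 1.062, 1.035 and 1.052, 1.031 and 1.003.

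**The case against.** The strongest reply is that the route to missing values is partly inferred. A reader might conclude that extubation ends EVLWI measurement and that LOCF therefore dilutes the effect and penalises a dose that speeds extubation. The document does not support this as a certainty. EVLWI is a thermodilution measurement, not a ventilator reading. The lung compliance, ventilation and driving pressure sections limit themselves to ventilated patients; the EVLWI section does not. Section {11b} has remaining procedures completed after treatment stops, and the schedule of activities (Fig. 2) is not available here. The plateau and placebo-death cases also show that dilution is only one possible outcome. This part of the reply stands.

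A reader might also infer that LOCF costs power or gives misleading standard errors. It does not in the scenarios examined. Comparing LOCF with complete data is unfair, because no method has complete data once values are missing, and the repeated-measures model recovers essentially no power. The standard errors agree with the empirical spread. In the no-effect case with unequal leaving, the rejection rate was 6.1%, and the 0.34 ml/kg shift is about a tenth of the SD (0.34 / 3.5).

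Two further points limit the impact. The trial is a safety study sized on feasibility, with all efficacy analyses labelled preliminary. Details of sensitivity imputation are properly left to the SAP. What remains is that LOCF as the main method is the protocol's stated choice, not a matter deferred, and that its wording makes every alternative optional.

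Finally, a repeated-measures model has its own weakness: it assumes missing at random and in effect extrapolates EVLWI for patients who have died. That is correct, and it is why the fix has two parts.

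**Conclusion.** The point holds as one about bias of unpredictable direction. The protocol makes LOCF the main method for its key preliminary efficacy contrast, treats death and recovery alike, and requires no other analysis. If patients leave while EVLWI is falling, the planned 3.2 ml/kg becomes about 2.4 to 2.9 in the main scenarios, and the shrinkage is greater when solnatide patients leave earlier. If leavers have plateaued, there is no bias. If placebo has clearly more early deaths with high last values, the difference rises to about 3.5 to 3.9. Faster leaving alone, with no effect on EVLWI, yields about 0.3 ml/kg against solnatide.

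All these sizes rest on assumed exit rates, exit days and EVLWI courses. The document gives hospital mortality but no day-7 rate of death, extubation or missing values. LOCF cannot be assumed conservative here, so the reported difference would be hard to interpret either way. The change should be made, but the safety objective does not depend on it.

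**What to change.** - **Main analysis:** a mixed model for repeated measures on all post-baseline EVLWI values to day 7, with treatment cohort, day, treatment-by-day, baseline EVLWI and baseline-by-day. Report the day-7 contrast against placebo and keep the existing testing order.
- **Required sensitivity analysis:** rank deaths before day 7 as the worst outcome and compare cohorts on ranks, with a stated rule for survivors who have no day-7 value. Replace the permissive wording with a commitment. This must be mandatory because the main model extrapolates EVLWI for patients who died.
- **LOCF:** keep it as a further sensitivity analysis.
- **Reporting:** tabulate the reason for each missing day-7 value by cohort, so that the likely direction of bias can be judged.

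The cost is protocol and SAP wording and standard software. LOCF already presupposes interim EVLWI values, so no new measurements should be needed; confirm this against the schedule of activities. With 20 patients per active arm, a simpler covariance structure should be prespecified as a fallback. Little or no power is gained.

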#### Change from baseline to day 7 in Pulmonary Vascular Permeability Index (PVPI)

The absolute value and the change from baseline will be analyzed by treatment group for PVPI by means of summary descriptive statistics at each time point until day 7.

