**Table Taba:** 

Title {1}	Safety and preliminary efficacy of sequential multiple ascending doses of solnatide to treat pulmonary permeability edema in patients with moderate-to-severe ARDS - a randomized, placebo-controlled, double-blind trial
Trial registration {2a and 2b}.	Primary Registry and trial identifying number: clinicaltrialsregister.eu ; EudraCT 2017-003855-47 Date of registration in primary registry: 2 February 2018 Secondary identifying numbers: not applicable Sources of monetary or material support: Apeptico Forschung und Entwicklung GmbH Primary sponsor: Apeptico Forschung und Entwicklung GmbH Secondary sponsor(s): not applicable Contact for public queries: Apeptico Forschung und Entwicklung [name]. [name] [name] [name] [contact] Contact for scientific queries: Apeptico Forschung und Entwicklung [name]. [name] [name] [name] [contact] Public title: Safety and preliminary efficacy of sequential multiple ascending doses of solnatide to treat pulmonary permeability edema in patients with moderate-to-severe ARDS - a randomized, placebo-controlled, double-blind trial Scientific title: Safety and preliminary efficacy of sequential multiple ascending doses of solnatide to treat pulmonary permeability edema in patients with moderate-to-severe ARDS - a randomized, placebo-controlled, double-blind trial Countries of recruitment: Austria, Germany Health conditions or problems studied: pulmonary permeability edema in patients with moderate-to-severe ARDS Interventions: Bronchial inhalation of ascending doses of solnatide vs. placebo for seven days Key inclusion and exclusion criteria: Ages eligible: ≥ 18 years Sexes eligible: both Accepts healthy volunteers: no Inclusion criteria: diagnosis of moderate to severe ARDS according to the Berlin definition, need for mechanical ventilation, pulmonary edema (EVLWI ≥10 ml/kg PBW), informed consent Exclusion criteria: allergy against solnatide, severe septic shock, extracorporeal membrane oxygenation at time of screening Study type: interventional allocation: randomized intervention model: parallel assignment masking: double blind (patient, caregiver, investigator, outcomes assessor) Date of first enrolment: 23.05.2018 Target sample size: 95 Recruitment status: ongoing Primary outcome: Safety (mortality, AEs, SAEs, laboratory data, ECG) Key secondary outcomes: extravascular lung water index (EVLWI), pulmonary vascular permeability index (PVPI), oxygenation ratio, ventilation parameters

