## Objectives {7}

The main objective is to assess the local and systemic safety of 7 days orally inhaled sequential multiple ascending doses of solnatide in patients with pulmonary permeability edema and moderate-to-severe ARDS.

Secondary objective is to review potential efficacy endpoints for a future Phase III pivotal trial.

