### Outcomes {12}

The main objective of this study is to investigate the safety of solnatide administration. Therefore, no formal primary and secondary outcomes are defined. Safety will be assessed by a review of mortality, incidence of adverse events, and serious adverse events, as well as by analysis of relevant laboratory data and ECG. The following parameters will be taken into account when assessing the safety of solnatide:
Vital signs (i.e., heart rate, systolic and diastolic blood pressure, and temperature)Clinical laboratory (i.e., white and red blood cell count, hematocrit, hemoglobin concentration, platelet count, creatinine, sodium, potassium, chloride, blood urea nitrogen, bilirubin, aspartate and alanine transaminases, lactate dehydrogenase, amylase, lipase, C-reactive protein, creatine kinase, arterial pH, PaO_2_, PaCO_2_, bicarbonate, SO_2_ as well as urine pH, specific weight, appearance, color, nitrites, proteins, glucose, urobilinogen, bilirubin, ketones, hematic pigments, and leukocytes)12-lead electrocardiogramHemodynamic parameters (i.e., mean arterial pressure, pulmonary blood volume, cardiac index, and cardiac outputNeed for vasoactive drugs24-h fluid balanceConcomitant medicationsAll-cause deathsUtilization of extracorporeal treatmentsAdverse events and serious adverse events

The secondary objective of this study is to evaluate possible endpoints for a future Phase III pivotal trial. Such endpoints investigated in this study include:
Extravascular lung water indexPulmonary vascular permeability indexMurray lung injury scoreOxygenation ratioVentilation parameters (i.e., plateau pressure, tidal volume, positive end-expiratory pressure, peak inspiratory pressure, respiratory rate, F_i_O_2_, mean airway pressure, peak airway pressure, ventilation mode)Lung complianceVentilation-free daysDays of ICUDays of hospitalizationDriving pressureSequential organ failure assessment

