#### Sequential Organ Failure Assessment (SOFA)

The absolute value and the change from baseline will be analyzed for SOFA score by means of summary descriptive statistics at each time point until day 7.

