#### Oxygenation ratio (P_a_O_2_/F_i_O_2_ ratio)

The absolute value and the change from baseline will be analyzed for oxygenation ratio (P_a_O_2_/F_i_O_2_) by means of summary descriptive statistics at each time point during first 7 days.

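### Outside EVLWI and ventilator-free days, the candidate Phase III endpoints get by-arm tables only: no placebo difference, interval or baseline adjustment is planned for PVPI, PaO2/FiO2 or SOFA

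*Protocol article*

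**What the plan says.** The objective appears twice. Objectives {7}: "Secondary objective is to review potential efficacy endpoints for a future Phase III pivotal trial". Outcomes {12}: "The secondary objective of this study is to evaluate possible endpoints for a future Phase III pivotal trial". The registration table under Administrative information lists: "Key secondary outcomes: extravascular lung water index (EVLWI), pulmonary vascular permeability index (PVPI), oxygenation ratio, ventilation parameters".

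Statistical methods {20a} sets the status of this work: "All efficacy analysis will be considered as secondary preliminary efficacy analyses". It also states "A two-sided alpha level 0.05 will be considered", with no adjustment for multiple comparisons among these variables. Continuous data are to be summarised by mean, SD, median, quartiles and extremes. A difference between arms and a confidence interval are not on that list.

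The methods by endpoint are:

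- **EVLWI**: ANCOVA on change to day 7, with baseline as covariate and cohort as factor, compared with placebo.
- **Ventilator-free days**: ANOVA on cohort, compared with placebo, no covariate.
- **PVPI**: value and change "will be analyzed by treatment group for PVPI by means of summary descriptive statistics at each time point until day 7".
- **SOFA**: value and change "will be analyzed for SOFA score by means of summary descriptive statistics at each time point until day 7".
- **PaO2/FiO2**: value and change analysed "by means of summary descriptive statistics at each time point during first 7 days".
- **Murray score, lung compliance, ventilation parameters, driving pressure**: descriptive.
- **Time to extubation, ICU days, hospital days**: descriptive.

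What the article leaves to the SAP is narrower: censoring rules, extra imputation for EVLWI, and subgroup analyses. The choice of method for PVPI, PaO2/FiO2 and SOFA is made here.

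**The concern.** To judge whether an endpoint is a good candidate for Phase III, one asks how far solnatide moves it relative to placebo, how precisely that is known, and what residual SD a later trial would be sized on. For three of the four registered key secondary outcomes (PVPI, oxygenation ratio, ventilation parameters) no such contrast is planned. The reader is left to compare columns of raw means by eye.

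Two things are lost. The imprecision of each comparison is not shown, although it is large with 20 patients per dose. Chance differences at baseline also go straight into the raw changes, since randomisation is unstratified and nothing in the analysis corrects for them. The model that would deal with both is already specified for EVLWI, and the baseline values are already needed for the change scores.

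**Working it through.** **The plan's own figure.** Sample size {14} gives about 80% power for EVLWI with 20 per group, difference 3.2 ml/kg, SD 3.5, two-sided 0.05, t-test. The noncentrality is 3.2 / (3.5 × √(1/20 + 1/20)) = 3.2 / 1.107 = 2.89 on 38 df, which gives 80.4%. It reproduces. The article gives no effect, SD or correlation for PVPI, PaO2/FiO2 or SOFA, so what follows is in units of the day-7 SD.

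**Assumptions.** Baseline/day-7 correlation r = 0.3 to 0.7. Ratio of baseline SD to day-7 SD, k, either 1 (equal SDs) or 0.5 to 0.6. The second case is plausible for PaO2/FiO2, because entry at 200 mmHg or below truncates the baseline.

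**Variance.**

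- Change score: 1 + k² − 2rk
- ANCOVA: 1 − r²
- Ratio: (1 − r²) / (1 + k² − 2rk), which is (1 + r)/2 when k = 1

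| r | k = 1 | k = 0.6 | k = 0.5 |
|---|---|---|---|
| 0.3 | 0.65 | 0.91/1.00 = 0.91 | 0.91/0.95 = 0.96 |
| 0.5 | 0.75 | 0.75/0.76 = 0.99 | 0.75/0.75 = 1.00 |
| 0.7 | 0.85 | 0.51/0.52 = 0.98 | 0.51/0.55 = 0.93 |

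The variance saving is therefore 15% to 35% with equal SDs, and 0% to 9% with a compressed baseline.

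**Chance imbalance.** The standard error of a baseline difference is √(1/20 + 1/20) = 0.32 baseline SD for 20 against 20, and √(1/20 + 1/35) = 0.28 for 20 against 35. Given an imbalance of d baseline SDs, the raw-change contrast is shifted by |k − r| × d day-7 SDs. For a one-standard-error imbalance:

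- k = 1: from 0.3 × 0.28 = 0.08 to 0.7 × 0.32 = 0.22 SD
- k = 0.5 to 0.6: from 0 (when k = r) to 0.3 × 0.32, about 0.10 SD

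ANCOVA removes this shift when the linear model holds.

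**Precision of a planned contrast.** The 95% half-width is t × residual SD × √(1/n₁ + 1/n₂), with df from the two groups compared. The residual SD is √(1 − r²) for ANCOVA and, at k = 1, √(2(1 − r)) for the change score.

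| Comparison | Method | r = 0.3 | r = 0.5 | r = 0.7 |
|---|---|---|---|---|
| 20 vs 35 | change (k = 1) | 0.67 | 0.56 | 0.44 |
| 20 vs 35 | ANCOVA | 0.54 | 0.49 | 0.40 |
| 20 vs 20 | change (k = 1) | 0.76 | 0.64 | 0.50 |
| 20 vs 20 | ANCOVA | 0.61 | 0.55 | 0.46 |

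Both placebo totals are shown because Trial design {8} gives 1:1 for the third step (10 + 5 + 20 = 35 on placebo), while the section on sequence generation {16a} gives 4:1. With 20 on the high dose, 4:1 would make it 10 + 5 + 5 = 20. The two passages must be reconciled; the point stands either way.

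**The case against.** The strongest reply is that this is a safety trial sized on feasibility, whose efficacy analyses are all declared preliminary. Modelling two endpoints and describing the rest is a recognised choice at 20 per dose. More intervals, over several endpoints and three doses with no multiplicity control, invite selective reading. This stands as a reason against tests and significance claims. It does not justify leaving out the estimate and its interval, because side-by-side means invite the same selective reading and hide the uncertainty.

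Four stronger readings are tempting, and the article does not support them.

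- **That the plan cannot show which endpoint responds.** The tables hold the randomised placebo arm, with mean and SD of change. If the number assessed is printed, as it usually is, an unadjusted difference and interval follow, and the SD of change is available for sizing.
- **That selecting on PaO2/FiO2 and EVLWI thresholds biases the comparison through regression to the mean.** Placebo patients enter under the same thresholds, so on average it affects every arm alike. Only chance imbalance and precision remain.
- **That a variance saving of 15% to 35% is established.** It needs equal SDs at baseline and day 7, which the article does not give, and it can shrink to almost nothing.
- **That baseline adjustment is missing everywhere it belongs.** Time to extubation, ICU days and hospital days have no baseline value to adjust for.

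It is also fair to say that the EVLWI model cannot simply be copied. It runs on data with last observation carried forward, whereas {20a} applies no missing-data method to the other endpoints. An adjusted day-7 estimate without a word on who is in it could look more authoritative than it is. That has to be met in the fix.

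**Conclusion.** The concern holds as a mismatch between objective and method. The article sets out to evaluate candidate endpoints, then fixes by-arm description for PVPI, PaO2/FiO2 and SOFA, so their response to solnatide can be compared only informally and without correction for baseline imbalance. It is not a detail awaiting the SAP.

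The loss is moderate: an explicit contrast with its interval, plus some efficiency. Under the assumed correlation of 0.3 to 0.7, ANCOVA variance is 0.65 to 0.85 of the change-score variance with equal SDs, and about 0.91 to 1.00 if the baseline SD is 0.5 to 0.6 of the day-7 SD. None of these inputs is in the article. No conclusion about safety, the EVLWI analysis or the ventilator-free-days analysis is affected.

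**What to change.** Keep every descriptive table. For PVPI, PaO2/FiO2 and SOFA at day 7, add the ANCOVA specified for EVLWI (baseline as covariate, treatment cohort as factor) and report:

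- each dose-minus-placebo difference with its 95% confidence interval;
- the residual SD;
- per cohort, the number analysed, the number missing through death and the number missing for other reasons.

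Label these estimates exploratory, with no hypothesis tests. Base them on available assessments, as {20a} already provides, and say that they describe patients still measured at day 7. Where they stand beside EVLWI, note that EVLWI uses carried-forward values.

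Compliance, driving pressure and ventilation parameters should stay descriptive. They are summarised only in patients still ventilated, a selection after randomisation that baseline adjustment does not remove. So one registered key secondary outcome, ventilation parameters, remains without a contrast, for a stated reason. The change does not apply to time to extubation, ICU days or hospital days.

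The cost is a few lines of protocol or SAP text and an adapted program, with no new data or patients. The downside is a few more exploratory intervals, and wide ones.
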